# Practice facilitation to implement stepped care for unhealthy alcohol use in HIV clinics: study protocol for a type III hybrid effectiveness-implementation study

**DOI:** 10.1186/s13722-026-00662-6

**Published:** 2026-03-31

**Keywords:** Alcohol, Screening, Alcohol use disorder treatment, Practice facilitation, HIV

## Abstract

**Background:**

Despite availability of evidence-based alcohol reduction interventions (EBIs), unhealthy alcohol use (UAU) remains a barrier to HIV medication adherence, viral suppression, and retention in HIV care. While translation of alcohol EBIs into HIV clinical practice is important for comprehensive HIV care, their implementation in HIV settings is impeded by resource constraints, workflow challenges, and negative perceptions of alcohol-related care.

**Methods:**

Guided by the Consolidated Framework for Implementation Research and Reach, Effectiveness, Adoption, Implementation and Maintenance frameworks, we will conduct a Hybrid Type 3 effectiveness-implementation study testing whether external practice facilitation increases reach, adoption, implementation, and maintenance of stepped care for UAU in three Center for AIDS Research (CFAR) Network of Integrated Clinical Systems (CNICS) HIV clinics in the United States. We will secondarily test whether practice facilitation is associated with clinical outcomes. We will first conduct a mixed methods formative evaluation to tailor delivery of practice facilitation (including the tools, technical assistance, and content expertise offered) based on each site’s context and needs (Aim 1). We will then deliver practice facilitation across the three sites sequentially to implement a stepped-care model of alcohol treatment to patients with UAU. Stepped care, where non-responders to alcohol EBIs are offered a more intensive therapy, will specifically include person- or computer-delivered brief alcohol intervention, on-line cognitive behavioral therapy, and linkages to alcohol pharmacotherapy. Clinical outcomes will include: (1) clinic-level implementation outcomes of stepped care EBIs for alcohol use including reach, adoption, maintenance, using mixed methods (Aim 2a) and (2) patient-level outcomes using interrupted time series analysis with synthetic controls (Aim 2b). Finally, we will use summative evaluation to describe barriers and facilitators to implementation of the interventions at each site to describe maintenance and inform widespread sustainable implementation (Aim 3).

**Discussion:**

This trial tests an implementation strategy to improve the delivery of stepped care, an evidence-based treatment approach for UAU in HIV clinics. Practice facilitation has shown promise for implementing evidence-based care for UAU in primary care but use of practice facilitation for this purpose in HIV clinics is novel. Results from this implementation study may support broader implementation of alcohol evidence-based practices in HIV care.

**Trial registration:**

The trial is registered with Clinicaltrials.gov, identifier NCT05241990 Date of submission 2/16/2022.

## Background

At-risk or unhealthy alcohol use (UAU), a spectrum of alcohol use ranging from exceeding weekly or daily recommended limits to alcohol use disorder (AUD) [1], is prevalent among persons with HIV (PWH), with over 25% endorsing patterns of unhealthy use [2]. UAU disrupts critical steps in the HIV Care Continuum, including antiretroviral therapy (ART) use, ART adherence, and viral suppression [3–7]. UAU also complicates the management of other medical conditions, including cardiovascular, and liver disease, and increases the risk for certain malignancies, including breast, colon, and head and neck cancer [8]. Given that UAU is a modifiable barrier to optimal clinical outcomes among PWH, increasing access to and uptake of evidence-based alcohol reduction strategies is an essential component of comprehensive HIV care.

Though alcohol screening and brief intervention are recommended for primary care [9], most patients do not receive these services [10, 11]. Further, most people in need of alcohol treatment do not access traditional treatment services citing barriers of cost, concerns of stigma or a negative effect on their job, and lack of knowledge of where to get treatment [12, 13]. As such, integration of evidence-based interventions (EBIs) for alcohol reduction in HIV clinics may address an important need and help to overcome common barriers. Studies among PWH support brief alcohol intervention (computer and person-delivered), motivational interviewing, cognitive behavioral therapy, and pharmacotherapy as effective EBIs for reducing alcohol use [14–21]. In a study conducted in two university-based HIV clinics (Birmingham, Alabama and Seattle, Washington), tablet-based alcohol screening combined with a computer-delivered brief intervention significantly reduced drinks per week among PWH with UAU [22]. In addition, stepped care, where non-responders to initial treatment were escalated to more intensive approaches, was effective in reducing alcohol use and improving viral suppression among United States (US) Veterans with HIV and AUD [23].

Implementation of EBIs for UAU in clinical settings is challenged by provider- and clinic-level barriers including lack of time and resources, inconsistent screening, inadequate training in managing UAU, operational workflows, and low confidence in the use of alcohol pharmacotherapy [24]. Practice facilitation is a multilevel intervention implementation strategy that addresses barriers to implementation of evidence-based practices. With practice facilitation, a practice coach offers tools, resources, hands-on guidance, and content expertise to assist the team in developing strategies to successfully implement an evidence-based practice [25–27]. Support by a practice coach is provided in near-real time and optimized by relationship development with each clinic site. There is substantial evidence in favor of practice facilitation in primary care, and multiple studies are using practice facilitation to implement alcohol EBIs [23, 25, 27–30]. Based on evidence in primary care settings [31, 32], practice facilitation for implementing alcohol EBIs may hold great promise for improving access to care in HIV clinics.

We are conducting a novel study in HIV clinics in which we will test practice facilitation to implement stepped care for UAU. In this manuscript, we describe the protocol of our Hybrid Type 3 effectiveness-implementation study guided by the RE-AIM (Reach, Effectiveness, Adoption, Implementation and Maintenance) evaluation framework [33]. Our study tests whether external practice facilitation increases reach, adoption, implementation, and maintenance of stepped care for UAU (our clinical intervention) in three Center for AIDS Research (CFAR) Network of Integrated Clinical Systems (CNICS) HIV clinics. We will secondarily test whether practice facilitation is associated with decreased UAU and improved ART adherence and viral suppression at the patient level (**e**ffectiveness). Formative and summative evaluations – guided by the Consolidated Framework for Implementation Research (CFIR) [34] - will also be used to tailor the implementation supports provided throughout the trial and characterize barriers and facilitators to implementation.

## Methods

This protocol follows reporting procedures outlined by the Standards for Reporting Implementation Studies (StaRI) statement [35].

### Implementation context

All implementation activities are nested within CNICS, a longitudinal, multi-site clinical cohort study of adults ≥ 18-years-old with HIV enrolled in care. An electronic health record (EHR)-based network, CNICS integrates clinical data from a large and diverse population of PWH across ten academically-affiliated HIV clinics in the US [36].CNICS prospectively collects comprehensive patient data, including validated health outcomes, across a range of diseases, as well as detailed patient reported outcomes (PROs) and behaviors at the time of clinical visits [37]. Through regular computer-based PRO administration, delivered at approximately six-month intervals, patients report on symptoms and behaviors, including alcohol use, using the Alcohol Use Disorders Identification Test-Consumption (AUDIT-C), the AUDIT, and the MINI International Neuropsychiatric interview alcohol domain (MINI) [38–40], with responses summarized and shared with providers. The PROs provide a foundation on which to embed EBIs into clinical care sites and to collect outcomes. CNICS sites have staff responsible for administration of the PRO who can link individuals to an intervention. Activities for the current study occur at three geographically diverse CNICS sites located in Boston, Massachusetts, Chapel Hill, North Carolina, and San Diego, California with a prevalence of unhealthy alcohol use ranging from 23% to 33%.

### Conceptual framework and logic model

The design of this implementation study is guided by the Consolidated Framework for Implementation Research (CFIR) and the RE-AIM evaluation framework [41–43]. The CFIR identifies five domains of implementation and several sub-domains which can be used to identify implementation barriers, devise strategies to optimize implementation, and evaluate the effectiveness of implementation efforts [33]. The domains encapsulated in the CFIR and depicted as “determinants” in Fig. 1 include: (1) characteristics of the clinical intervention, (2) individuals using it, the (3) outer and (4) inner settings in which implementation occurred, and (5) the implementation process. In alignment with Smith et al.‘s methodology [44] for planning, executing, reporting, and synthesizing implementation projects, our framework applies the determinants to all aspects of the study, including the implementation strategy we have chosen (practice facilitation), barriers and facilitators to implementation overall, the success of the implementation strategy particularly, and the mechanisms through which we anticipate that practice facilitation will foster successful implementation of the clinical intervention, alcohol EBIs. The RE-AIM framework is applied to ascertainment of our outcomes, which are also determined by the CFIR domains through implementation work.

**Fig. 1 Fig1:**
[figure not shown]
Revised logic model, based on implementation learnings

### Implementation strategy: practice facilitation

In this Hybrid Type 3 implementation-effectiveness study [45], we are testing practice facilitation as the implementation strategy. Practice facilitation uses multiple discrete implementation strategies supported by a practice coach (internal or external) who offers flexible supports throughout the implementation period that are tailored to local context (e.g., to each site) [46, 47]. The primary objective of practice facilitation is to foster internal capacity for change within a clinical setting. In practice facilitation, practice coaches assist clinical teams in identifying gaps in care and facilitate the team’s development of a plan to address those gaps. This often involves activities of education or knowledge brokering, technical assistance, coaching, expert consultation, and other supports as identified by the local site [48].

For this study, we are providing the three clinics with an external Practice Coach, a person outside of their organization who has expertise in alcohol-related care, practice improvement approaches, and implementation science. The same practice coach will work with each site. In addition, sites will assemble a Local Implementation Team (LIT), an interdisciplinary group of local clinical and administrative champions with the shared goal of implementing the clinical intervention. While each LIT will be expected to have a combination of clinical and administrative research champions, the specific membership of and communication pathways used with each LIT may vary based on the local context of each site.

Practice facilitation will be delivered to each clinic over an 18-month implementation period. The implementation period is organized around three phases of implementation: *pre-implementation*, *implementation*, and *sustainment*. The Practice Coach and LIT will collaborate on implementation activities via regular teleconference meetings and ad hoc activities as described in Table 1, however activities will vary based on each site’s needs, preferences, and infrastructures. To promote continuous learning and adaptation by the implementation team, each clinic’s implementation period is staggered across the study so that their *pre-implementation* phases begin approximately one year apart from one another.

**Table 1 Tab1:** Implementation and practice facilitation activities over the implementation period

Implementation Phase	Implementation Objectives	Anticipated Practice Coach Activities
*Pre-implementation* (3 months)	• Adapt workflows and/or clinic resources to accommodate delivery of stepped care for UAU • Train & prepare staff on clinical delivery of stepped care for UAU	• Facilitation of bi-weekly meetings with LIT • Identification and preparation of local champions • Identification, development, and/or delivery of training resources • Facilitation of design session and/or focused meetings to design and/or refine workflows for delivery of stepped care for UAU
*Implementation* (12 months)	• Deliver stepped care for UAU within clinic	• Facilitation of monthly meetings with LIT • Real-time delivery of monitoring and feedback data on implementation progress • Facilitation of process improvement approaches (e.g., Plan, Do, Study, Act (PDSA)) • Technical assistance to design and/or refine implementation support materials (e.g., patient and/or provider-facing materials that support implementation)
*Sustainment* (3 months)	• Establish plan for long-term integration and monitoring of stepped care practices in clinic	• Facilitation of monthly meetings with LIT • Technical assistance to develop sustainment plans that address the person, technical, and leadership resources needed to sustain stepped care long-term

### Clinical intervention

The clinical intervention (stepped care) includes clinic-based alcohol use screening, followed by alcohol reduction EBIs delivered through a stepped care approach.

#### Screening

As part of routine clinical care, PWH undergo tablet-based, PRO screening with the AUDIT-C approximately every six months. Based on validated cut-points (AUDIT-C scores ≥ 3 for women or ≥ 4 for men), administration of the 10-item AUDIT will be triggered in the PROs. Women with AUDIT scores ≥ 5 and men ≥ 6 then receive the MINI International Neuropsychiatric Interview alcohol domain (MINI) [38] to assess for AUD. When a patient screens positive for UAU, a staff member designated by the site will receive an automated alert via pager with the recommended intervention based on UAU severity. The patient is then approached, consented, and linked to an EBI if they are interested. This system has been programmed into the CNICS PRO platform from earlier work [22].

#### Interventions

(see Fig. 2). The specific alcohol EBI offered to each patient is determined by the absence or presence of AUD and AUD severity. Individuals with UAU and either no AUD or mild AUD are offered a brief alcohol intervention, while individuals with moderate to severe AUD are offered alcohol pharmacotherapy and cognitive behavioral therapy in addition to a brief intervention. The alcohol EBIs include computer (CBI) [22]- or person-delivered brief intervention, on-line cognitive behavioral therapy (CBT4CBT) [49], and alcohol pharmacotherapy. The CBIs, described in our prior work [21], use cognitive behavioral techniques for alcohol reduction or cessation. The sessions are delivered in a motivational interviewing style by a 3-D virtual counselor. Four sessions tailored to levels of alcohol severity and session number (initial vs. follow-up) (Table 2) have been developed. All CBI sessions have also been scripted to be delivered in-person and by Zoom. CBT4CBT is an online cognitive behavioral therapy program consisting of seven modules, 45 min each in length, which include refusal skills, recognizing and coping with cravings, addressing thoughts about alcohol use, patterns of thinking, and decision making around alcohol use. Finally, alcohol pharmacotherapy includes Federal Drug Administration (FDA) approved therapies for alcohol use, including naltrexone and acamprosate.

**Fig. 2 Fig2:**
[figure not shown]
Alcohol stepped care approach

**Table 2 Tab2:** Description of computer-delivered interventions and pharmacotherapy

Intervention	Inclusion	Description
CBI Prime	PWH with UAU or mild AUD at visit 1	Includes education about standard drink sizes, patterns/spectrum of alcohol use, decisional balance exercises, and the impact of alcohol on HIV, comorbidities, and medication adherence. It also presents common moods or situations for drinking and offers strategies for coping with these. Patients have the opportunity to set drinking goals
CBI Pharma	PWH with moderate/severe AUD at visit 1	Includes CBI Prime content, an overview of pharmacotherapy options, and how they may help with drinking reductions or abstinence
CBI Problem	PWH who maintained or increased UAU at visit 2 after receiving CBI Prime at visit 1	Discusses possible barriers to reduction, coping strategies, and the use of alcohol pharmacotherapy
CBI Prize	PWH who reduced UAU to lower risk use at visit 2	Reviews patients’ experiences in reducing their alcohol use, identifies successful strategies, reviews risky drinking, coping strategies, and provides an opportunity to set new drinking goals
CBT4CBT	PWH with moderate to severe AUD at visit 1 or visit 2	Online CBT program consisting of seven modules, 45 min each, that include refusal skills, recognizing and coping with cravings, addressing thoughts about alcohol use, patterns of thinking, and decision making around alcohol use
Alcohol pharmacotherapy	PWH with moderate to severe AUD at visit 1 or visit 2	FDA approved therapies for alcohol use, including naltrexone and acamprosate

*Stepped care procedure*: For PWH with UAU without moderate to severe AUD based on screening, CBI Prime will be delivered by computer or person based on clinic site or patient preference. For those with moderate to severe AUD, PWH will receive CBI Problem (computer or person delivered) tailored to higher alcohol use severity that includes information on pharmacotherapy. In addition, they are provided with three options: CBT4CBT, alcohol pharmacotherapy, or both. At their next scheduled clinic visit (within ~ 4–6 months), PWH will undergo the PRO, and they will receive a second intervention based on this follow-up AUDIT-C score. PWH who continue to drink at unhealthy levels will be stepped up to a higher level of care and receive CBI Problem that reinforces alcohol pharmacotherapy and addresses medication adherence barriers. They will also be offered CBT4CBT and alcohol pharmacotherapy (see Fig. 2). Those with alcohol below unhealthy levels receive a brief intervention with affirming messages via CBI Prize.

As part of the design of the trial, clinics can choose to offer flexible options for the delivery of alcohol EBIs including CBI, face-to-face with a provider, or telemedicine. These modalities will vary both within and between clinics dependent on clinic and patient preferences and capacity. A staff member selected by each site, who could be a social worker, behavioral health specialist, or another appropriate professional depending on the clinic’s structure and staff availability, will facilitate interventions. Clinic operations will be pragmatic, and thus, it is possible staff will turn over during the study period. During the practice facilitation period, the practice facilitator will be available to support sites through any barriers that arise, including staff turnover.

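### The stepped-care text and Table 2 give incompatible rules on which session, and which treatment offers, some patients receive

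*Protocol article*

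**What the plan says.** The Interventions section sets a general principle: "The specific alcohol EBI offered to each patient is determined by the absence or presence of AUD and AUD severity". It also reports that four computer-delivered brief intervention (CBI) sessions were developed. Table 2 names them Prime, Pharma, Problem and Prize.

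The stepped care procedure then gives the sequence.

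- **Visit 1, moderate to severe AUD:** "For those with moderate to severe AUD, PWH will receive CBI Problem (computer or person delivered) tailored to higher alcohol use severity". These patients also choose between CBT4CBT, pharmacotherapy or both. CBI Pharma is not named anywhere in the procedure.
- **Visit 2:** "they will receive a second intervention based on this follow-up AUDIT-C score". Further, "PWH who continue to drink at unhealthy levels will be stepped up to a higher level of care and receive CBI Problem", and of the same patients, "They will also be offered CBT4CBT and alcohol pharmacotherapy".

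Table 2 states who is included for each component.

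- **CBI Pharma:** "PWH with moderate/severe AUD at visit 1".
- **CBI Problem:** "PWH who maintained or increased UAU at visit 2 after receiving CBI Prime at visit 1".
- **CBT4CBT and alcohol pharmacotherapy, identical entries:** "PWH with moderate to severe AUD at visit 1 or visit 2".

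**The concern.** Two parts of the same article describe the clinical intervention, and for some patients they cannot both be followed. The disagreement covers the session a patient is given and, at visit 2, whether a patient without moderate to severe AUD is offered CBT4CBT and medication at all.

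Under Screening, a designated staff member receives an automated alert carrying a recommended intervention. That presupposes a single rule, and the article states two. The second Implementation measure in Table 3, the share of treatment sessions completed, also needs a statement of which sessions were due. With two rules there are two candidate denominators.

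**Working it through.** The plan gives no figure on this point, so there is nothing to reproduce. The check sets the procedure text beside Table 2 for each patient state. A state is defined by AUD severity at visit 1 and, at visit 2, by whether unhealthy use continued and by AUD severity then.

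| State | Procedure text | Table 2 | Agree? |
|---|---|---|---|
| Visit 1, no or mild AUD | Prime | Prime | Yes |
| Visit 1, moderate/severe AUD | Problem; CBT4CBT and drug offered | Pharma; CBT4CBT and drug offered | Session differs |
| Visit 2, from no/mild, use continued, still no/mild | Problem; CBT4CBT and drug offered | Problem; neither offered | Offers differ |
| Visit 2, from no/mild, use continued, now moderate/severe | Problem; both offered | Problem; both offered | Yes |
| Visit 2, from no/mild, use reduced | Prize | Prize | Yes |
| Visit 2, from moderate/severe, use continued, now no/mild | Problem | No session listed | Session differs |
| Visit 2, from moderate/severe, use continued, still moderate/severe | Problem | No session listed | Session differs |
| Visit 2, from moderate/severe, use reduced | Prize | Prize | Yes |

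Four of these eight rows disagree. That ratio depends on how the states are cut and says nothing about how many patients fall in each, so it does not measure importance. The disagreements reduce to three.

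1. **Visit 1, moderate/severe AUD.** The session name differs. The offers of CBT4CBT and pharmacotherapy agree.
2. **Visit 2, continued use after moderate/severe AUD at visit 1.** The text gives CBI Problem. Table 2 requires prior CBI Prime, which these patients did not have under either source, and lists nothing else for them. Read literally, the text also gives them the same named session twice while calling the second a step up, but that follows from the name in item 1 and is not a separate fault.
3. **Visit 2, continued use, no moderate/severe AUD at either visit.** The text acts on the AUDIT-C score and offers both treatments. Table 2 excludes these patients from both. The general principle in the Interventions section, which refers to AUD presence and severity, matches the form of Table 2's rule and not an AUDIT-C rule. That shows a conflict within the article; it does not settle which rule was meant.

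**Effect on sessions due, per patient, through visit 2**

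- Item 1: one CBI session at visit 1 under either name, so the count is the same.
- Item 2: text 1 + 1 = 2 CBI sessions; Table 2 1 + 0 = 1.
- Item 3: Prime plus Problem, 1 + 1 = 2 CBI sessions under both. If CBT4CBT modules count as sessions (an assumption; Table 3 does not say) and the patient accepts the offer, the text gives 2 + 7 = 9, using the seven modules stated in the article, against 2 under Table 2.

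**Effect on other outcomes.** The primary outcome counts patients who report any alcohol intervention. Reach counts any evidence-based intervention. The prescribing measure has all clinic providers as its denominator. The other effectiveness outcomes rest on AUDIT-C, viral load and adherence. The power statement uses monthly autocorrelation. None needs to know which session was assigned.

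**The case against.** **It is a naming slip.** For visit 1 this is plausible. The procedure describes that session as suited to higher severity and as covering pharmacotherapy, which resembles Table 2's entry for CBI Pharma. Reading it so removes item 1. It does not supply a visit-2 session in Table 2 for item 2, and it does not touch item 3, which concerns eligibility.

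**Table 2 only describes the components; the procedure governs.** This has some force for item 2, where Table 2 is too narrow but names no competing session. It has less force for item 3, because the table has an inclusion column and that column excludes patients whom the text includes.

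**Flexibility is intended.** The flexibility described is about mode of delivery (computer, face to face or telemedicine). It does not extend to which session is due or who is offered medication.

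**Figure 2, or the full protocol, may settle it.** Figure 2 is not visible here and could show the intent. It could not make the text and the table agree. Nor is this a detail left out for brevity: two rules are stated.

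**A stronger reading.** A reader might infer that sites, starting about a year apart, will deliver different versions of care, so that the exploratory by-site analysis would confuse version of care with the coach's growing skill. The article does not support this. The alert system is programmed on the shared CNICS PRO platform from earlier work, and the same coach works with every site. Nothing points to site-specific versions.

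**Conclusion.** The inconsistency is real and needs correcting, but its reach is limited. Items 2 and 3 remain even if item 1 is a slip, and item 3 is the most consequential because it decides whether a group of patients is offered CBT4CBT and medication.

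Statistically, one non-primary measure is affected: the percentage of sessions completed has no unique set of sessions due. How far it would move cannot be calculated, because the article does not give the number of patients in each state, the uptake of offers, or whether modules count as sessions. It would be wrong to infer that the primary analysis is compromised, since the primary outcome, Reach, the prescribing measure and the power statement can all be obtained under either version.

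The conclusion rests on reading the text and Table 2 as both current, and on the visit-2 wording meaning what it says. It takes no view on which assignment is clinically right.

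**What to change.** Reconcile the Interventions section, Table 2, the stepped care procedure and Figure 2 into one pathway. It should cover every combination of visit-1 AUD severity, visit-2 response and visit-2 AUD severity, giving for each the session due and whether CBT4CBT and pharmacotherapy are offered. It should also state whether the visit-2 decision turns on AUDIT-C alone or also on AUD severity. The clinical team decides the content.

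Then confirm that the alert programmed in the PRO platform follows that pathway, and define the denominator for sessions completed from it, saying whether CBT4CBT modules count.

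The cost is protocol wording and one check of the alert logic. No change to the design, the primary outcome or the power statement is needed.
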